## Methods/design

### Recruitment and study design

This prospective, randomized, single-center, pilot study on intermediate- and high-risk prostate cancer patients is ongoing at Asan Medical Center. Patients are randomized into two groups with a 1:1 allocation using blocked randomization, and the random block size is 4. The randomization sequence is generated by the clinical research nurse using Excel software. The allocation sequence is concealed from the primary investigator who enrolls the patients using the Excel file locked with a password. Also, the file is saved in a computer located in the place that the primary investigator cannot approach. One group will receive a CyberKnife SBRT boost dose of 18 Gy administered in three fractions (18-Gy group), and the other group will receive a CyberKnife SBRT boost dose of 21 Gy administered in three fractions (21-Gy group).

As shown in Fig. 1, all patients will first receive ADT. Several studies strongly support the use of ADT in addition to EBRT, long-term (i.e., 2–3 years) ADT for high-risk patients [13, 14] and short-term ADT (4–6 months) for the intermediate group [15, 16]. Risk group definition is based on the current National Comprehensive Center Network guidelines (https://www.nccn.org/professionals/physician_gls/pdf/prostate.pdf). Informed consent of patients is mandatory before recruitment and is obtained from the radiation oncologists. Three months after the start of ADT, WPRT (44 Gy in 20 fractions) with intensity-modulated radiotherapy (IMRT) will be initiated. Next, CyberKnife boost will be implemented. Since the primary investigator has to confirm the plan for CyberKnife boost, the blinding is not possible afterward.

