For SBRT boost planning, another non-enhanced CT with 1.25-mm slices will be obtained at 1 week before the start of the boost therapy. Patients will be in a supine position with a vacuum cushion and an ankle pillow and with an empty bladder and a Foley catheter inserted for delineation of the urethra. The rectal balloon will not be used for the boost therapy. Boost volume is identical to the GTV of WPRT delineation, whereas the PTV margin is 3 mm in all directions. The urethra as well as the rectum and bladder are also included in the OAR. The CyberKnife robotic radiosurgery system (Accuray Incorporated, Sunnyvale, CA, USA) will be utilized for the SBRT boost, and the PTV must receive ≥ 80% and < 120% of the prescribed dose. OAR dose constraints are as follows: (1) rectum, < 85% of prescription dose; (2) bladder and urethra, < 100% of prescription dose. Prescription doses are 18 Gy and 21 Gy in three fractions, every other day. Tracking for fiducial markers will be used for image-guided radiotherapy. An enema will be performed for bowel preparation before every treatment. The whole radiotherapy period will not exceed 10 weeks.

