### Data collection and follow-up period

Patient data will be collected before start of radiotherapy, every week during WPRT, at the end of WPRT, at the end of SBRT boost, and at 1-month and 4-month follow-up visits after radiotherapy (Fig. 2). Patient data will be documented in Case Report Forms on urologic/gastrointestinal toxicities using the Common Toxicity Criteria for Adverse Events (CTCAE v 4.03), patient-reported outcomes (PRO), and PSA levels. After confirmation of the CyberKnife boost plan (at fourth week of radiotherapy), the evaluation of toxicities and efficacy will be no longer be blind. For ADT initiation, patients will be evaluated by the Department of Urology during follow-up visits every 3 months. After radiotherapy sessions, patients will also be evaluated by the Department of Radiation Oncology every 3 months for the first 2 years, every 6 months until 5 years, and annually thereafter. Follow-up evaluations will assess chronic toxicities and PSA levels. If clinical recurrence is suspicious, imaging studies, such as MRI and/or bone scans, will be considered.

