### Assessment of primary and secondary endpoints

Primary endpoints of this trial are acute toxicities and short-term biochemical control. Acute toxicities are defined as events occurring within 3 months after treatment and are evaluated according to the CTCAE v 4.03 and PRO, using the Overactive Bladder Symptom Score and the International Prostate Symptom Score. Secondary endpoints are chronic toxicities and long-term biochemical control. Chronic toxicities are evaluated using the Late Effects of Normal Tissues scoring system. Biochemical recurrence (BCR) is defined as the Phoenix consensus definition of a rise in PSA level by 2 ng/ml or more above the nadir value [19].

The trial design and protocol adhere to the Recommendations for Interventional Trials (SPIRIT) criteria. The SPIRIT Checklist and Figure can be found in Additional file 1: Table S1 and Fig. 2.

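### Blinding is abandoned when one investigator approves the boost plan, although that reason unmasks only that investigator and patients could stay unaware of 18 versus 21 Gy

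*Protocol article*

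**What the plan says.** All references are to the protocol article.

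- **Reason for ending blinding** (Recruitment and study design): "Since the primary investigator has to confirm the plan for CyberKnife boost, the blinding is not possible afterward".
- **When it ends, and for what** (Data collection and follow-up period): "After confirmation of the CyberKnife boost plan (at fourth week of radiotherapy), the evaluation of toxicities and efficacy will be no longer be blind".
- **Endpoints** (Assessment of primary and secondary endpoints): "Primary endpoints of this trial are acute toxicities and short-term biochemical control". Acute toxicity covers events within 3 months after treatment and is "evaluated according to the CTCAE v 4.03 and PRO, using the Overactive Bladder Symptom Score and the International Prostate Symptom Score".
- **Treatment before the boost** (Recruitment and study design), the same for everyone: "Three months after the start of ADT, WPRT (44 Gy in 20 fractions) with intensity-modulated radiotherapy (IMRT) will be initiated".
- **The boost** (Treatment implementation): "Prescription doses are 18 Gy and 21 Gy in three fractions, every other day". The planning CT, urethral catheter, enema and fiducial tracking are described once, for all patients.
- **Readings** are taken before radiotherapy, weekly during pelvic treatment, at its end, and then "at the end of SBRT boost, and at 1-month and 4-month follow-up visits after radiotherapy".

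The article does not say whether patients are told their boost dose, or who grades CTCAE.

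**The concern.** The conclusion is wider than the reason given for it. One investigator needs to see the dose, and from this the article concludes that blinding as a whole is impossible and that evaluation of toxicity and efficacy is open from then on. Nothing in the stated reason reaches the patient, who completes the Overactive Bladder Symptom Score (OABSS) and the International Prostate Symptom Score (IPSS), or a clinician who grades CTCAE without having approved the plan.

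The timing makes this matter. Masking covers treatment that is common to both arms and lapses before the treatment that separates them.

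The exposed measures are part of a primary endpoint, and they are subjective. A patient or grader who knows that the dose was the higher one may report or grade more toxicity. A grader who favours escalation may grade less. The direction cannot be known in advance, so it cannot be corrected afterwards. The Discussion relies on patient reports because clinicians may miss or underestimate toxicity, so patient awareness of dose would weaken the instrument meant to compensate. The results are to inform a phase II study that selects the boost dose, and a distorted toxicity contrast would carry into its design.

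**Working it through.** The article gives no figure for masking, so there is none to reproduce. The check is a comparison of its sections, followed by an illustration of scale.

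**1. Whom does the stated reason unmask?** The person who approves the plan. Treatment staff will also know the dose, and the research nurse who generates the allocation sequence already does. Patients and other graders are not on this list.

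**2. When do the arms first differ?** Pelvic treatment is 44 Gy in 2.2-Gy fractions every weekday: 44 / 2.2 = 20 fractions, and 20 / 5 = 4 weeks. Plan confirmation falls in the fourth week of radiotherapy, so it precedes the boost.

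| Reading | Can show a dose difference? | Masking provided? |
|---|---|---|
| Before and during pelvic treatment, up to plan confirmation | No, same treatment | Yes |
| End of boost | Yes | No |
| 1 month | Yes | No |
| 4 months (after the 3-month acute window) | Yes | No |

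**3. Could a patient tell the arms apart?** Both have three fractions, every other day, on the same system with the same preparation. The dose per fraction is 18 / 3 = 6 Gy or 21 / 3 = 7 Gy. Nothing described would reveal this to a patient who is not told. The article gives no session times; I assume that any difference would not be recognisable to someone who sees only his own sessions.

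**4. Which endpoints are exposed?** OABSS and IPSS are completed by the patient and CTCAE is a clinical grading, so both can be moved by expectation. Biochemical control rests on PSA, a laboratory value, and is much less exposed.

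**5. Scale, under assumptions only.** Inputs from the article: 15 per group and Fisher's exact test. Assumed: two-sided 0.05, no true dose effect, a true event rate *p* of 20%, 30% or 40%, and open reporting that adds *b* to the rate in one arm. The rejection probability is the sum, over all tables (i, j) with Fisher p ≤ 0.05, of Bin(i; 15, p) × Bin(j; 15, p + b).

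| Added by open reporting | p = 20% | p = 30% | p = 40% |
|---|---|---|---|
| 0 points | 1.7% | 1.7% | 1.6% |
| 10 points | 4.0% | 3.4% | 3.3% |
| 20 points | 11.2% | 9.7% | 9.5% |
| 30 points | 24.6% | 22.7% | 22.7% |

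For a symptom score shifted by *d* standard deviations (normal approximation), the chance of rejection in the direction of the shift is Φ(d√(15/2) − 1.96):

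- d = 0.25: Φ(0.685 − 1.96) = Φ(−1.275) = 10.1%
- d = 0.50: Φ(1.369 − 1.96) = Φ(−0.591) = 27.7%

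With no shift, the rate in one direction would be 2.5%. In a descriptive pilot the estimate matters more than the test, and the estimated difference absorbs the whole of *b* or *d*.

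**The case against.** The strongest reply is that the article never says patients are unmasked. The first statement concerns the primary investigator, and the second, that "the evaluation of toxicities and efficacy will be no longer be blind", most naturally describes the evaluators. An article may leave the details of masking to the full protocol. This stands in part. A reader might infer that patients are told their dose and that the patient-reported scores are open as a matter of fact; the document does not support stating that. What it does support is that blinding is declared impossible without qualification and that no masking of patients or graders is provided afterwards. If patients are in fact kept unaware, the two statements are too broad and need correcting.

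Four further points stand and limit the concern:

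- It does not reach every primary outcome, because PSA is little affected.
- The 4-month visit lies after the 3-month acute window, so it should not be counted as a primary acute reading.
- A separate masked CTCAE grader may need staff time, and the article does not describe who is available.
- A tempting remedy, making the patient-reported comparison the lead one, would be a mistake. OABSS and IPSS are urinary scores, whereas gastrointestinal toxicity is recorded by CTCAE.

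It can also be said that this is a purely exploratory pilot that openly declares when blinding ends. That lowers the stakes. It does not supply the missing reason, and the results are still meant to inform the phase II design.

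**Conclusion.** The point holds in limited form. The reason given for ending blinding applies to the investigator who approves the plan, and the article draws from it a general loss of blinding just before the arms diverge. The subjective acute-toxicity measures at the end of the boost and at 1 month, and the toxicity readings at the later 4-month visit, therefore have no stated protection against expectation bias. On the treatment as described, much of that protection was available.

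The size of the bias cannot be established from the document. The rejection rates shown rest on assumed event rates and assumed shifts, and indicate scale only. With 15 per group, a shift of plausible size could not be told from a dose effect. The verdict rests on two readings: that the unqualified wording may include patients, and that nothing in the delivery reveals the dose. It is a worthwhile improvement to an exploratory pilot, not a flaw that invalidates it.

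**What to change.** Restate both blinding passages (Recruitment and study design; Data collection and follow-up period) to say:

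1. Only the investigator who approves the plan and the treatment staff are unmasked by plan confirmation, in addition to the nurse who holds the allocation list.
2. Patients are not told their boost dose until the acute-toxicity assessments are complete, with unmasking if care requires it. Name the visit that ends masking, since the 3-month window and the 4-month visit do not coincide.
3. OABSS and IPSS are completed before contact with the clinician.
4. Where existing staff who did not approve the plan see the patient, they grade CTCAE without the dose shown. Otherwise CTCAE is reported as open-label.

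Keep CTCAE, including gastrointestinal toxicity, alongside the patient-reported comparison, with neither made subordinate.

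**Cost:** items 1 to 3 need protocol and consent wording and an unmasking provision. The dose must be kept out of patient-facing papers, which is a small burden. Item 4 uses only staff who already see the patient and may need some coordination. Recruitment was not complete at publication, so patients not yet boosted could benefit. Report separately any patient who already knew the dose.

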**Fig. 1 Fig1:**
[figure not shown]
Flowchart of treatments for the trial. ^*^Risk group defined as per National Comprehensive Center Network (NCCN) guidelines

The dose schedules are designed to achieve the biological effective dose (BED) as that of the conventional regimen with 78 Gy administered in 38 fractions. BED is widely used in radiation oncology to compare diverse radiation dose regimens using different fraction sizes, fraction numbers, and total doses [17]. For calculation of BED, an α/β ratio constant, i.e., the dose at which cellular death rates with linear and quadratic components are equivalent, is needed. A usual α/β ratio for normal tissue is 3, whereas that for prostate cancer is 1.5. As summarized in Table 1, the normal tissue BED for conventional regimen is 130.0 Gy, which is similar to that for the boost regimen of 18 Gy (130.7 Gy) and lower than that for a boost regimen of 21 Gy (146.7 Gy). The BED values for prostate cancer are 182.0, 197.3, and 226.3 Gy with conventional, 18-Gy boost, and 21-Gy boost therapies, respectively. As result, the 18-Gy group will receive the same BED for adjacent organs, while the tumor will receive 110% BED of conventional EBRT, while the 21-Gy group will be irradiated 110% and 120% BED of conventional EBRT for normal organ and prostate cancer, respectively.

**Table 1 Tab1:** Biological effective dose (BED) calculations

	Conventional dose (78 Gy/28 fractions)	18-Gy group	21-Gy group
Normal tissue BED^a^ (Gy)	130.0	130.7	146.7
Prostate cancer BED^a^ (Gy)	182.0	197.3	226.3

^a^α/β ratio for normal tissue is 3, and 1.5 for prostate cancer

### Inclusion criteria

Patients fulfilling the following criteria are eligible for this trial: age, 20 years or older; diagnosis of pathologically confirmed intermediate- or high-risk prostate cancer within 6 months after enrollment; and an Eastern Cooperative Oncology Group performance status of 0–1. Patients should also fulfill the following biochemical and laboratory criteria based on tests performed within 6 months before enrollment: absolute neutrophil count, ≥ 1500 cells/mm^3^; platelet count, ≥ 50,000 cells/mm^3^; hemoglobin, ≥ 8.0 g/dl; normal kidney function within 6 months before enrollment as determined by creatinine < 2.0 ng/dl; normal liver function within 6 months before enrollment as determined by total bilirubin < 1.5 times the maximum normal value; alanine aminotransferase or aspartate aminotransferase < 2.5 times the maximum normal value.

### Exclusion criteria

Patients who fulfill the following criteria are excluded from this trial: distant metastasis; pelvic lymph node metastasis; history of ADT within 6 months before enrollment; history of definitive treatment for prostate cancer such as radical prostatectomy; history of pelvic irradiation; diagnosis of double primary cancer other than skin or thyroid cancer.

### Dropout criteria

Patients who desire to exit the trial or withdraw consent will be dropped out of the study. Additionally, any medical issues as well as unexpected serious complications occurring during treatment or the follow-up period that hinder completion of the study protocol will result in patient dropout.

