### Statistical analysis

The present study is being performed as a purely exploratory pilot study; therefore, by calculation for statistical analysis, a total 15 patients in each treatment group is considered as an appropriate sample size. Comparison of the treatment two groups will be conducted using the chi-square test or Fisher’s exact test. Biochemical recurrence-free survival (BCRFS) will be calculated from the ADT start date using the Kaplan-Meier method. Descriptive statistics of all analyzed parameters will be provided, whenever appropriate.

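### The dropout rule lets follow-up end because of the toxicity being measured, since it does not separate stopping treatment from leaving the study

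*Protocol article*

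**What the plan says.** The Dropout criteria section of the protocol article gives two routes out of the study. The first is the patient's wish to leave or withdrawal of consent. The second is added to the first and has the same result: medical issues, and the statement that "unexpected serious complications occurring during treatment or the follow-up period that hinder completion of the study protocol will result in patient dropout". The second route is open during treatment and during follow-up.

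The section on primary and secondary endpoints says "Primary endpoints of this trial are acute toxicities and short-term biochemical control", and "Acute toxicities are defined as events occurring within 3 months after treatment". It adds that "Secondary endpoints are chronic toxicities and long-term biochemical control".

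Under Data collection and follow-up period, data on toxicity, patient-reported outcomes and PSA are collected before radiotherapy, then "every week during WPRT, at the end of WPRT, at the end of SBRT boost, and at 1-month and 4-month follow-up visits after radiotherapy". Late visits follow every 3 months for 2 years, every 6 months until 5 years, and yearly after that.

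Under Statistical analysis, "a total 15 patients in each treatment group is considered as an appropriate sample size", and "Comparison of the treatment two groups will be conducted using the chi-square test or Fisher’s exact test". The article does not say whether a patient who drops out is still assessed, whether the complication behind the dropout is counted, or whether the patient stays in the denominator.

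**The concern.** A serious complication that stops a patient from completing the protocol is itself an event for a primary endpoint (if acute) or a secondary endpoint (if chronic). The rule uses that event to end the patient's participation, so missing data would depend on the outcome.

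Nor is the rule limited to stopping radiotherapy. It continues into follow-up, when radiotherapy is over. Apart from continuing ADT, the main thing left to end at that stage is the assessment itself.

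Whether a complication hinders completion is a judgement. The article says that assessment is no longer blind once the boost plan is confirmed in the fourth week of radiotherapy, which is before any dose-related difference between the arms can appear.

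The pilot's toxicity and short-term PSA results will be used to design the phase II study that selects the boost dose. Incomplete toxicity data on the worst-affected patients would weaken that use.

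**Working it through.** **1. What dropout removes, by timing.** Setting the dropout rule beside the assessment schedule:

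- Dropout during WPRT: the remaining weekly assessments, the end-of-WPRT and end-of-boost assessments, the 1- and 4-month visits, and all late follow-up are at risk.
- Dropout after the boost but before 1 month: both follow-up visits that cover the 3-month acute window are at risk, together with their patient-reported and PSA data.
- Dropout later: chronic toxicity and long-term biochemical control are at risk. In the first 5 years this is up to 24/3 + 36/6 = 8 + 6 = 14 scheduled visits.

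In each case the triggering event may already be on the case report form. What can be lost is everything after it, including a worse grade of the same toxicity.

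**2. The plan's own figures.** The 15 per group cannot be reproduced, because no error rate, power, event rate or dropout rate is given. The point does not depend on it. One patient in an arm is 1/15 = 6.7 percentage points.

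The ground for expecting more toxicity at 21 Gy is the stated normal-tissue BED, 130.7 Gy against 146.7 Gy: a gap of 16.0 Gy, or 146.7/130.7 = 1.12. Recalculated from the schedules with α/β = 3:

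- 18 Gy: 44 × (1 + 2.2/3) + 18 × (1 + 6/3) = 76.3 + 54 = 130.3
- 21 Gy: 44 × (1 + 2.2/3) + 21 × (1 + 7/3) = 76.3 + 70 = 146.3

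These are each 0.4 below the stated values, with the same gap of 16.0 Gy.

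**3. Effect if dropped patients also left the denominator.** This is a conditional calculation; the article does not say it would happen. Let p be the true rate of serious toxicity and f the share of affected patients removed from numerator and denominator. The observed rate is p(1 − f)/(1 − pf). With assumed true rates of 10% (18 Gy) and 30% (21 Gy) and the same f in both arms:

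| f | 18 Gy | 21 Gy | Difference (points) |
|---|---|---|---|
| 0 | 10.0% | 30.0% | 20.0 |
| 25% | 7.7% | 24.3% | 16.6 |
| 50% | 5.3% | 17.6% | 12.4 |
| 75% | 2.7% | 9.7% | 7.0 |
| 100% | 0% | 0% | 0 |

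Differences are taken before rounding. With assumed rates of 10% and 20%, the difference of 10 points falls to 8.1, 5.8, 3.2 and 0. With equal rates of 10%, the difference stays 0, but both arms show 5.3% at f = 50%.

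**4. In counts (assumed).** 1/15 against 5/15 is 6.7% against 33.3%, a difference of 26.7 points (Fisher p = 0.17). If one affected patient at 18 Gy and three at 21 Gy are removed, this becomes 0/14 against 2/12, a difference of 16.7 points (p = 0.20).

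**5. Effect if the event is counted over all 15.** The bias for that event is zero. The loss of later assessments in step 1 remains.

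**The case against.** The strongest reply is that the rule says patients drop out and nothing more. It does not say that data are discarded or that the event goes uncounted. Toxicity is recorded often enough that a complication serious enough to cause dropout would ordinarily be on file already. The analysis set and the handling of dropouts usually belong in the full protocol or the SAP, neither of which is shown. This stands. A reader might infer that the worst toxicities leave the analysis, but the article does not say so.

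The trigger is also narrower than all serious complications: they must be unexpected and must hinder completion. Expected or manageable toxicity would not qualify. This stands too, although the wording on medical issues is not limited to unexpected or serious ones.

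A reader might further infer that the rule makes 21 Gy look safer than it is. The documents do not support that as a conclusion. Planned treatment differs between the arms only in the three boost fractions, so complications before the boost are not related to boost dose. The BED values make more events at 21 Gy plausible but do not establish them. Even then, removing the same share of affected patients in each arm, at rates like those assumed, shrinks the difference toward zero without reversing it. To reverse it, the share removed would have to be higher at 21 Gy, and nothing in the article points to that. An example that removes two of three events at 21 Gy and none at 18 Gy (3/15 to 1/13, beside an unchanged 1/15) makes the arms look alike only because it treats them unequally.

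Finally, this is an exploratory pilot, and the dose will be selected in a later study. That limits the consequences. It does not answer the main point: the dropout rule is stated, not left open, and an SAP can define a denominator but cannot supply assessments that were never made.

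**Conclusion.** The point holds in this form: the rule ends participation on the same footing as withdrawal of consent, and the trigger can be the primary or secondary endpoint event itself. Followed as written, it puts at risk the rest of the 3-month acute window, the 1- and 4-month CTCAE, patient-reported and PSA data, and chronic toxicity in the patients affected.

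Understatement of serious toxicity is conditional. It requires that dropped patients are left out of the denominator, or that later events go unrecorded. Shrinkage of the difference between the arms also requires more such events at 21 Gy. All rates, counts and removal shares in the calculation are assumptions, because the article gives none. At 6.7 points per patient, the loss of one to three affected patients would be material to an arm's toxicity rate.

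**What to change.** Amend the Dropout criteria so that discontinuing study treatment and ending study follow-up are separate, without changing any clinical rule on when treatment stops:

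- A patient who discontinues treatment because of a medical issue or complication continues the scheduled toxicity, patient-reported and PSA assessments unless consent to them is withdrawn.
- Data collected up to any withdrawal are kept.
- The complication that triggers discontinuation is counted as a toxicity event in the allocated group, and patients who discontinue stay in the denominator.

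An additional analysis of all patients who started the boost would be reasonable for the dose contrast, provided that those who discontinue after starting it are kept in.

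The cost is a wording amendment and continued follow-up of a few patients at visits already scheduled, with no new patients or procedures. The article reports recruitment as not yet complete, so at that point the change could still protect data not yet collected.
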